During our previous work with Finnish schools [10], we learned that a major reason for poor school performance among refugee and non-refugee immigrant children lies in difficulties detecting the core reasons and mechanisms behind learning barriers. The reasons and mechanisms involve cognitive, social, and mental health issues that should be assessed early on and in combination with each other. Further, Nordic schools have varying, and often insufficient, knowledge and competence on how to relate appropriately to a diverse group of refugee students with multifaceted needs [8]. In Finland, adolescents with immigrant backgrounds are at greater risk of unmet needs for support and help at school than native-born Finnish adolescents [11] and teachers feel that immigrant students lack consistent support structures [12]. We need objective, universal, and user-friendly tools to assess different factors that explain children’s capacity to follow teaching or carry out their tasks at school, which are at the core of children’s integration into the education system. Profile-based scientific information about relative, age-specific differences across refugee, non-refugee immigrant, and native-born children regarding cognitive and social capacity and mental health is not available, and supportive actions are therefore often ineffective.

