## Methods

### Participants and procedure

The participants are a sample of 450 students aged 10–12 from primary schools in Southwest Finland. 150 children are refugees, 150 non-refugee immigrants, and 150 native-born Finnish schoolchildren. Schools are selected on the basis that they have a preparatory class where all asylum seekers and most non-refugee immigrants study for their first year after arriving in Finland. We will select one preparatory class and one regular class in each school to draft the sample for the study. The study has two time points: baseline measurements at the beginning of the school year (T_1_) and follow-up measurements at the end of the school year (T_2_). The study uses a screening battery tool to administer a variety of questionnaires and tests which are then used to give feedback about the students to teachers and multiprofessional student welfare bodies. We aim to collect all the data within one school year (2024–2025), but if the number of participants does not reach 150 in each group, a second round of data collection will take place in 2025–2026. We will conduct a small-scale pilot study in one preparatory and one regular class in Spring 2024.

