### Tests and measures

**Demographic variables.** At T_1_, we ask the children, as well as their parents, about the children’s age, class, gender, living arrangements, and country of birth. If the country of birth is not Finland, we ask how many years they have spent in Finland, with whom they came to Finland, immigration status, place of residence, and reason for migration. At T_2_, we ask about significant life changes after T_1_, including changes in legal status in host country, family composition, significant losses or other changes in close relations, and other significant life changes. The same kind of questionnaire was used in a previous study among refugee and native-born children in Finland [10, 33]. At T_2_, we collect a list of supportive actions the child thinks they have received during the school year.

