#### Cognitive functioning

**General intelligence** is measured with a matrix reasoning task. This task involves 15 trials, where participants are presented with a 3 × 3 matrix with a missing piece and four options for the missing piece to pick from to best complete the matrix. The 15 matrix items, ranging from easy to quite difficult, were selected from the Matrix Reasoning Item Bank [34] to provide adequate differentiation. The total number of correct choices is summed, with participants’ performance compared to each other, as no norms for this selection of items exist.

**Working memory** facilitates learning, comprehension and problem-solving as it allows an individual to keep information in mind and use it to execute cognitive tasks. Working memory is assessed by a digit span task, where the participant is shown numbers one at a time in sequences of increasing length. The participant then tries to repeat the sequence by clicking numbers on the screen.

**Self-regulation** is the ability of an individual to flexibly apply situational rules and adjust his/her actions and expectations. To succeed, individuals must follow legal and cultural rules, regulate impulses, and apply different rules depending on contexts. Self-regulation is measured with one task per each of the three dimensions of self-regulation: a) Inhibition, b) Shifting, and c) Updating. *Inhibition* is measured with the Go/NoGo task [35] involving the ability to prevent a response or impulse. Most trials are “Go” or “Button Press” trials, however on the rare “No Go” trials, individuals must inhibit a button press. *Shifting* is measured with the Colour Shape Task [36], involving shifting between tasks flexibly. Trials randomly alternate between classifying by shape or by color. *Updating* is measured with the Corsi Task [37], which requires adding and deleting information in working memory. In this task, boxes light up in sequences, and individuals must then correctly click them in the same sequence. Each level adds difficulty by adding another box to the next new sequence.

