#### Parental report

**Demographic variables.** At T_1_, we ask background information such as parents’ age, country of birth, education, marital status, and housing arrangements are collected. We also ask parents to report on the child’s country of birth, current legal status in host country, time in host country, and reason of migration. We request this information from both parents and children. Parents would be more reliable informants on these questions, but in the likely situation that we are unable to reach all parents, we will have the child’s report on the same topics. If there is discrepancy in child and parent reports, we rely on parents’ report. At T_2_, we ask about significant life changes after T_1_. The questionnaire includes changes in legal status in host country, family composition, significant losses, or other changes in close relations and other significant life changes. At T_2_, we collect information on whether or not the information provided by the SB has been used for the child, and a list of supportive actions the child or family has received.

**Family functioning** is measured by 12 items from the General Functioning subscale of the McMaster Family Assessment Device (FAD) [54, 55]. The parent assesses on a four-point scale how much they agree with the descriptions of family functioning (0 = s*trongly agree*, 1 = a*gree*, 2 = d*isagree*, 3 = s*trongly disagree*).

**Child language and development** is measured by 10 selected items from the Alberta Language and Development Questionnaire (ALDeQ) [56]. The selected items were chosen to reflect the parents’ view of the general development of the child and possible challenges in it, as well as parents’ own reading or learning difficulties. The parent evaluates each item on a four-point scale, but due to the varying form of the items, the answer categories vary between items (such as 0 = *never*, 1 = *rarely*, 2 = *sometimes*, 3 = *very much* or 3 = *very easy*, 2 = *easy enough*, 1 = *sometimes not easy*, 0 = *no, very hard*).

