#### Analysis plan

**Power.** In order to form profiles across different groups of children and to assess changes in cognitive, social, and mental health functions across those children who will receive SB based supportive actions and those who do not, we performed a preliminary power analysis to determine the sample size required to detect medium-sized or larger effects on these primary outcomes. Based on typical sizes of Finnish preparatory classes, we estimated the average size of each cluster to be 17, with a variance of 10. Intraclass coefficients for these outcomes are challenging to estimate, but based on our previous cluster-randomized research among war-affected children, values of 0.01–0.1 could be reasonable. With a relatively conservative estimate of 0.07 for the ICC, and setting alpha at 0.05, to achieve 80% power to detect a medium-sized (d = 0.5) or larger effect, we would need about 150 children in each group, meaning approximately 450 children in total.

**Analyses.** Means, standard deviations, and correlations will be evaluated for all variables reported by children, parents, and teachers. To test Hypothesis 1, baseline differences between the study’s three groups will be investigated using 3-way ANOVAs and followed up with *t*-tests to compare means. To test Hypothesis 2, correlation analyses will first be used to examine whether mental health (trauma-related and depressive symptoms) is associated with poorer cognitive function and social competence. Latent profile analyses (using the TidyLPA package in R) will then be run for the entire sample under each of the three dimensions: cognitive, social, and mental health. Emerging profiles will be compared with how they line up with our three groups (refugee, immigrant, native-born Finnish).

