To test Hypothesis 3, screening battery effects on cognitive, social, and mental health functioning will be evaluated using repeated measures ANOVAs with 2 × 3 for {T_1_, T_2_} and {children who received SB-based support, children who received non-SB-based support, children who did not receive SB-based support} among children who scored above/under critical thresholds, and following up with *t*-tests to compare means. Differences in SB-based actions will also be evaluated qualitatively. We will further use linear regression to test whether changes in mental health (trauma- and depressive symptoms) and social functioning associate with changes in cognitive functioning from T_1_ to T_2_. In addition to analyses in the whole sample, we will also do these analyses by subgroup, separately for our three groups. Classroom atmosphere, teacher self-efficacy and awareness of culturally responsive education, family functioning, child language and development as well as children’s cultural background will be used as covariates in the regression analyses and ANOVAs. Effect sizes and confidence intervals will be reported for main effects and p-value based inference will be de-emphasized based on guidelines for New Statistics [60].

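### Read literally, the Hypothesis 1 group ANOVAs adjust for an undefined cultural-background variable that overlaps group and for two parent-only scales, but not for age

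*Protocol article*

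**What the plan says.** Under Analysis plan, Hypothesis 1 is tested as follows: "baseline differences between the study’s three groups will be investigated using 3-way ANOVAs and followed up with *t*-tests to compare means". The groups are set by migration status under Participants and procedure: "150 children are refugees, 150 non-refugee immigrants, and 150 native-born Finnish schoolchildren".

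The covariates are named once, near the end of the same section. The sentence opens with "Classroom atmosphere, teacher self-efficacy and awareness of culturally responsive education, family functioning" and closes with "child language and development as well as children’s cultural background will be used as covariates in the regression analyses and ANOVAs". It does not exempt the Hypothesis 1 ANOVAs, and it does not list age.

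Three other places bear on this list:

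- **Parental report.** Family functioning and child language and development are both rated by the parent. The section anticipates incomplete contact ("in the likely situation that we are unable to reach all parents") and falls back on the child's answers, but only for the demographic and migration questions that both informants are asked.
- **Tests and measures, demographic variables.** Children and parents are asked about "age, class, gender, living arrangements, and country of birth". No variable called cultural background is defined here or elsewhere in the article.
- **Cognitive functioning.** The matrix reasoning total is a raw count of correct answers, with "performance compared to each other, as no norms for this selection of items exist".

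**The concern.** A covariate list fixes what a group contrast means and which children contribute to it. This one raises three problems for the adjusted Hypothesis 1 ANOVA.

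1. Cultural background overlaps the group factor. If native-born children hold a level that no other child holds, the model cannot separate group from background. Software will usually drop a column and print an estimate that depends on the coding.
2. Two covariates exist only where a parent responded. If children without them are dropped, the comparison rests on families the study could reach. The language and development items are also meant to capture the child's general development, which lies close to the cognitive outcome, so adjusting for them can absorb part of the difference being sought.
3. Age is left out, although one main cognitive outcome is an un-normed raw score in children aged 10 to 12. The Background section itself names the missing knowledge as "relative, age-specific differences across refugee, non-refugee immigrant, and native-born children".

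At stake is whether the adjusted analysis of the first hypothesis answers the question posed, in the children recruited.

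**Working it through.** **The plan's own figure.** Inputs from the Power paragraph: d = 0.5, alpha 0.05 (taken as two-sided), power 80%, mean cluster size 17 with variance 10, ICC 0.07.

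- Without clustering: 63 children per group.
- Design effect, equal clusters: 1 + 16 × 0.07 = 2.12, giving 134 per group.
- Design effect, unequal clusters: 1 + [(1 + 10/17²) × 17 − 1] × 0.07 = 2.161, giving 137 per group. That is 137/17 = 8.06 clusters, so 9 whole clusters, or 153 children.
- The stated figure of about 150 is therefore reproduced. It was calculated without covariates.

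**Estimability.** Take an intercept, two group indicators and, for illustration, a five-level culture variable (four indicators): 7 columns for 450 children.

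| Pattern of culture levels | Rank | Refugee-native | Immigrant-native | Refugee-immigrant |
|---|---|---|---|---|
| Finnish level only in native-born; migrant cultures overlap | 6 of 7 | not estimable | not estimable | estimable |
| No overlap between any groups | 5 of 7 | not estimable | not estimable | not estimable |
| Some native-born share migrant cultures | 7 of 7 | estimable | estimable | estimable |

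In the first row the native-born indicator and the Finnish-culture indicator are the same column. In the last row the native contrasts are carried by the native-born children who share a migrant culture.

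**Parent non-response.** The article gives no rate, so 20%, 30% and 50% are assumptions, applied equally to both groups compared, with complete-case analysis. With a fraction r retained, n = 150r, cluster size is 17r, and the design effect is DE = 1 + [(1 + 10/17²) × 17r − 1] × 0.07. Normal-approximation power is Φ(0.5 × √(n/(2·DE)) − 1.96). The last column uses a noncentral t with 2 × (150/17 − 1) = 15.6 degrees of freedom.

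| Non-response | n per group | DE | n/DE | Power, normal | Power, cluster-df t |
|---|---|---|---|---|---|
| 0% | 150 | 2.161 | 69.4 | 83.8% | 78.8% |
| 20% | 120 | 1.915 | 62.7 | 79.9% | 74.7% |
| 30% | 105 | 1.792 | 58.6 | 77.2% | 71.8% |
| 50% | 75 | 1.546 | 48.5 | 69.2% | 63.7% |

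At 30% the loss is 83.8 − 77.2 = 6.6 points (normal) or 78.8 − 71.8 = 7.0 (t). At 50% it is 14.6 or 15.1. The level depends on the method; the loss hardly does. If only one group is affected, normal-approximation power is 80.5% at 30% and 76.2% at 50%. None of these figures credits the covariates with reducing residual variance.

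**Age.** The bias in an unadjusted group difference is the age slope times the gap in mean age. The documents give neither. With assumed slopes of 0.2 to 0.4 SD per year:

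- gap of 0: no bias;
- gap of 0.25 year: 0.05 to 0.10 SD;
- gap of 0.5 year: 0.10 to 0.20 SD, against a design effect size of 0.5 SD.

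**The case against.** The strongest reply is that the pairwise comparison of refugee with native-born children is, as written, a t-test. The covariate sentence names regressions and ANOVAs, not t-tests. That comparison is identified, needs no parent questionnaire and drops no child. This stands. A reader might infer that the Hypothesis 1 comparison as a whole is not identified, and the text does not support that: only the adjusted ANOVA is affected. The reply also means that the ANOVA and its follow-up tests address different quantities, and that the t-tests adjust for nothing, age included.

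Other objections hold in part:

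- **Scope.** The covariate sentence follows the Hypothesis 3 and change analyses, where the factor of interest is type of support. It may have been meant for those. Its wording nevertheless covers all ANOVAs.
- **Group definition.** It is tempting to say that cultural background defines the groups. It does not; migration status does. Whether a contrast is aliased depends on a coding that the article does not give.
- **Missing data.** Loss of children follows only under complete-case analysis. The handling of missing data may be set out in a fuller plan.
- **Role of the parent scales.** Hypothesis 2 names mental health and social competence as the explanation, not these scales. The language and development items also cover parents' own reading or learning difficulties, which could act as confounders. That they would remove part of the effect is plausible, not certain.
- **Age.** The range is narrow, the immigrant comparison is described as being with children of the same age, and no imbalance is reported. A reader might infer that the comparison is confounded by age; the documents show only that nothing in the stated plan guards against it. The absence of norms is documented for the matrix task alone.

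**Conclusion.** The concern holds in limited form. As worded, the covariate list applies to the Hypothesis 1 ANOVAs and suits them poorly in three ways.

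- **Cultural background:** undefined and overlapping with group. Under the natural coding, with the Finnish level confined to native-born children, two of the three adjusted contrasts are not estimable.
- **Parent-only scales:** they would decide who enters the adjusted model if analysis is complete-case. The cost is roughly 7 to 15 points of power at an assumed 30% to 50% non-response, besides selection towards reachable families, and part of the cognitive difference may be adjusted away.
- **Age:** collected but not listed. No age matching is described, and refugee and native-born children are drawn largely from different class types (preparatory and regular), so balance cannot be taken for granted. The size of any bias is unknown.

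The non-response rates, age slopes and age gaps are assumptions. The overlap of cultural background with group, the parent-only source of the two scales and the absence of age from the list come from the article itself. The change is worth making before the planned preregistration.

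**What to change.** 1. State the main Hypothesis 1 model as group plus age and gender, fitted in all children, and take the follow-up pairwise comparisons as adjusted contrasts from that model instead of separate t-tests.
2. Define cultural background. Leave it out of any model that contains group, and use it descriptively or within the migrant groups.
3. Report the model with parent and teacher measures as a secondary, explanatory analysis, with missing parent data handled by multiple imputation.
4. Add age to the regressions of cognitive change on change in mental health and social functioning. The Hypothesis 2 correlations and latent profiles have no direct place for a covariate, so no change is asked for there.

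Age and gender are already collected, so no new data are needed. The sample size is unchanged because it was calculated without covariates. The cost is a revised paragraph and a little extra analysis, chiefly the imputation.

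### Covariates are attached to the ANOVAs and regressions but not to the follow-up t-tests, so as written the pairwise comparison of support types in Hypothesis 3 is unadjusted

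*Protocol article*

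**What the plan says.** All of this is in the Protocol article, Analysis plan.

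- **Hypothesis 1.** Baseline differences between the three groups of children (refugee, non-refugee immigrant, native-born) are examined "using 3-way ANOVAs and followed up with *t*-tests to compare means". No second or third factor is named.
- **Hypothesis 3.** Among children beyond the critical thresholds, a 2 × 3 repeated-measures ANOVA crosses time (T1, T2) with type of support, "following up with *t*-tests to compare means".
- **Covariates.** Classroom atmosphere, two teacher characteristics, family functioning, child language and development, and cultural background "will be used as covariates in the regression analyses and ANOVAs". The t-tests are not in that list.
- **Reporting.** Effect sizes and confidence intervals are promised for main effects, with less weight on p-values.

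The Research question section words both hypotheses as directed comparisons. Refugee children are expected to score below each of the other two groups. Battery-informed support is expected to help more than other support.

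**The concern.** An omnibus F test over three levels gives neither a direction nor a pair, so it cannot answer either hypothesis alone. Of the quantitative procedures stated for Hypotheses 1 and 3, only the follow-up t-tests compare the named pairs, and an ordinary t-test has no place for a covariate.

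The confidence intervals promised for main effects do not close the gap. Hypothesis 3 concerns a difference in change, which is a contrast within the time-by-support interaction. It is not a main effect.

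Support is not randomised. Schools plan it, and use of a child's individual results depends on a request and on parental permission (Feedback tool). Family functioning, classroom atmosphere and teacher self-efficacy could well differ between support groups, and the plan itself picks them as covariates. An adjusted F followed by raw comparisons could give two different answers, and the article has no rule for which one stands.

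**Working it through.** **1. The plan's own figure.** Inputs from the Analysis plan: "setting alpha at 0.05, to achieve 80% power to detect a medium-sized (d = 0.5) or larger effect"; ICC 0.07; cluster size 17 with variance 10. Two-sided testing is assumed.

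- Independent children: 2 × (1.96 + 0.842)² / 0.5² = 62.8, so 63 per group.
- Design effect with unequal clusters: CV² = 10/289 = 0.0346; 1 + ((0.0346 + 1) × 17 − 1) × 0.07 = 2.161.
- 63 × 2.161 = 136.2, so 137 per group by the normal approximation.
- With a t reference on cluster-level degrees of freedom, 9 clusters × 17 = 153 children give power 0.797.

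The stated figure of about 150 per group is therefore reproduced. The present point does not bear on it; d = 0.5 serves below only as a yardstick.

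**2. Which procedure gets covariates.**

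| Step | Named procedure | Covariates attached? | Answers the pairwise question? |
|---|---|---|---|
| H1 omnibus | ANOVA | Yes | No |
| H1 follow-up | t-tests | Not listed | Yes |
| H3 omnibus | 2 × 3 repeated-measures ANOVA | Yes | No |
| H3 follow-up | t-tests | Not listed | Yes |

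**3. What an unadjusted comparison could cost in H3 (illustration only).** The document gives no covariate imbalance, no covariate-outcome correlation and no support-group sizes. All three are assumed here.

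- D = difference in one covariate between two support groups: 0.3 to 0.5 SD.
- r = correlation of that covariate with the quantity compared: 0.2 to 0.4.
- n = 30 to 50 children per support group.

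Bias = D × r: 0.3 × 0.2 = 0.06 SD; 0.5 × 0.4 = 0.20 SD, which is 0.20/0.5 = 40% of the planned effect.

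Shift of the test statistic = bias × √(n/2). The table gives the two-sided rejection rate at 0.05 when the adjusted difference is zero, ignoring clustering.

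| n per group | Bias | Shift | Rejection rate |
|---|---|---|---|
| 30 | 0.06 | 0.232 | 5.6% |
| 30 | 0.20 | 0.775 | 12.1% |
| 50 | 0.06 | 0.300 | 6.0% |
| 50 | 0.20 | 1.000 | 17.0% |

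**4. The limit on that illustration.** H3 compares change, so r must be the covariate's correlation with T1-T2 change, and the bias is then in SDs of change. A stable group difference that moves T1 and T2 equally cancels. With r = 0 for change, bias = D × 0 = 0 and the rejection rate stays at 5%. The range for one covariate is therefore 0 to 0.20 SD under these assumptions. A wider grid (0.1 to 0.5 SD of outcome per SD of covariate, imbalance 0.2 to 0.8 SD) gives 0.1 × 0.2 = 0.02 to 0.5 × 0.8 = 0.40 SD, subject to the same limit.

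**5. What adjustment costs in precision.** For one covariate and two equal groups, the standard error changes by about √(1 + D²/4) × √(1 − r²).

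- D = 0.5, r = 0.2: 1.031 × 0.980 = 1.01.
- D = 0.5, r = 0.4: 1.031 × 0.917 = 0.95.

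The loss is small when overlap with group is modest. It grows as a covariate comes close to defining the group.

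**The case against.** The strongest reply is that the article does not say the t-tests use raw means. A follow-up to an ANOVA with covariates can be a contrast of that model's adjusted means, and an article may leave that detail to the full plan. This stands in part: that the comparisons are certain to be unadjusted is an inference. But the article does more than stay silent. It names the follow-up test and lists the procedures that receive covariates, and the test is not among them. Followed literally, the text yields an unadjusted comparison.

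A reader might infer three stronger things that the document does not support.

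- **That the t-tests decide the hypotheses or are the reported result.** They are described only as follow-ups, and the plan plays down p-values. The illustrative false-positive rates should be read with that in mind.
- **That the plan claims these covariates remove confounding.** It does not. Its wording about control (Aims and objectives; Research question) concerns significant life changes, which are not in this covariate list. That is a separate matter.
- **That raw Hypothesis 1 contrasts are the confounded ones.** Hypothesis 1 is a comparison of existing groups, not a treatment effect. Cultural background lies close to the group definition. Each school contributes one preparatory and one regular class (Participants and procedure), so classroom and teacher variables may track group too. Adjusting for them could remove part of the difference under study, so demoting raw means to description would be wrong.

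The label 3-way ANOVA is a slip: the text makes clear that three groups are compared. It needs correcting but adds no weight to the covariate point.

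**Conclusion.** The point holds in a limited form. As written, the covariates do not reach the procedure that compares the named pairs. This matters for Hypothesis 3, where the comparison is pairwise, concerns change and is not randomised. Its estimate is unadjusted on a literal reading and can disagree with the adjusted omnibus test.

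The size of any bias cannot be computed from the document and could be negligible or substantial. The 0 to 0.20 SD range, and rejection rates of up to 17.0%, rest wholly on assumed imbalance, correlation with change and group sizes. They illustrate what could happen and do not estimate this study's error.

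For Hypothesis 1 the defect is that the intended contrast is not stated. The document does not show that the unadjusted contrast is wrong.

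**What to change.** **Hypothesis 3.** Replace the follow-up t-tests with contrasts of T1-T2 change from the same covariate-adjusted repeated-measures model: SB-based minus non-SB-based support, and each against no support, every contrast with a 95% CI. Let each covariate act on change (a covariate-by-time term), because a covariate main effect alone leaves the change contrast unadjusted when data are complete. This takes the third support level to mean no support; its present label would also cover children given non-SB-based support, so the intended meaning should be stated.

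**Hypothesis 1.** Name a one-factor model with three levels in place of the 3-way ANOVA. Take the pairwise contrasts (refugee minus immigrant, refugee minus native-born) from that model with 95% CIs, and report unadjusted and adjusted versions side by side. Leave out of the adjusted version any covariate that nearly defines the group, such as cultural background, and name the omitted covariates in advance.

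**Cost.** A few sentences in the Analysis plan, no new data, a little more analysis, and slightly wider intervals where covariates overlap with group.

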We will also examine whether the supportive actions are reflected in cognitive, social, and mental health functions of refugee children within their first year in Finnish schools (after controlling for other significant life changes during the study year). We will investigate whether this effect is different compared to non-refugee immigrant children and/or native-born Finnish children and if the effect is different compared to actions not using the information produced by the screening battery. We hypothesize 3) that supportive actions informed by the findings of the screening battery have a stronger positive effect than other actions. Finally, we will examine whether improvements in mental health (trauma, depression, resilience) and social functioning during the school year are associated with better performance in cognitive tests.

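### Hypothesis 3 is about a difference in T1-to-T2 change between two kinds of support, but the plan promises estimates for main effects and never names that contrast

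*Protocol article*

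**What the plan says.** The Research question section states Hypothesis 3 as "that supportive actions informed by the findings of the screening battery have a stronger positive effect than other actions", and asks "if the effect is different compared to actions not using the information produced by the screening battery". The comparison is therefore SB-based against non-SB-based support. The Power paragraph also speaks of assessing changes.

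For this hypothesis, the Analysis plan says that "screening battery effects on cognitive, social, and mental health functioning will be evaluated using repeated measures ANOVAs", crossing T1 and T2 with three support levels: "children who received SB-based support, children who received non-SB-based support, children who did not receive SB-based support". The analysis is made "among children who scored above/under critical thresholds", "and following up with *t*-tests to compare means". The last sentence of the section covers reporting: "Effect sizes and confidence intervals will be reported for main effects and p-value based inference will be de-emphasized". The time-by-support term and the SB-based versus non-SB-based difference in change are not mentioned.

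**The concern.** A 2 × 3 repeated measures ANOVA answers several questions, and only one of them is Hypothesis 3. The plan promises estimates for the main effects, which answer others. Because it also plays down p-values, the reported estimates and intervals are what readers will take as the result.

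Support is not allocated at random. Schools plan it, and individual reports need a request and parental permission (Background; Feedback tool). Children who get SB-based support may therefore differ at T1 from those who get other support, and the support main effect would mix that difference with any effect of the support. The omnibus interaction has a different problem: it can reject because support of either kind beats no support, which says nothing about whether using the SB matters.

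**Working it through.** **Inputs from the document.** Two time points, three support levels, alpha 0.05 (taken as two-sided), and 0.5 SD as the effect size of interest (Power paragraph).

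**Assumptions not in the document.** 50 children per support group; SD 1 at each time; T1-T2 correlation r = 0.5, with 0.7 as a range; no clustering or covariates; the third level read as no support. The document does not say how many children will pass the thresholds or fall in each support group.

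**The plan's own figure.** The stated 150 per group (d = 0.5, ICC 0.07, mean cluster size 17) can be reproduced. A t-based cluster calculation gives 151 with equal cluster sizes and 154 allowing for the stated variance of 10. It concerns sample size and does not bear on this point.

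**What each term estimates.** Let group g have T1 mean a_g and change c_g.
- Support main effect: compares a_g + c_g/2. For SB-based minus non-SB-based support this is (a_SB − a_other) + (c_SB − c_other)/2: the baseline gap in full, the benefit in change halved.
- Time main effect: the average of c_g over the three groups.
- Omnibus interaction: 2 df; null c_SB = c_other = c_none.
- Hypothesis 3 contrast: 1 df; c_SB − c_other.

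This is algebra and holds for any sample size or correlation. The rates below illustrate it, using noncentral F and t. The SD of change is √(2(1 − r)) = 1.00 or 0.775. The SD of the two-occasion average is √((1 + r)/2) = 0.866 or 0.922.

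**Both kinds of support work equally (changes 0.5, 0.5, 0), so Hypothesis 3 is false.** Omnibus noncentrality = 50 × [2(1/6)² + (1/3)²] / SD² = 8.33 / SD², which is 8.33 at r = 0.5 and 13.89 at r = 0.7. Rejection: 73% and 92%. The direct contrast has a true null here and rejects about 5% of the time.

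**Hypothesis 3 true (changes 0.5, 0, 0).** Direct contrast: 0.5 / (SD × √(2/50)) = 2.50 or 3.23, power 70% or 89%. Support main effect: the difference shrinks to 0.25, noncentrality 50 × 0.25² × (2/3) / SD² = 2.78 or 2.45, power 29% or 26%.

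**No difference in change, SB group lower at both times.** Support main effect, noncentrality 50 × gap² × (2/3) / SD²:

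| Gap | r = 0.5 | r = 0.7 |
|---|---|---|
| 0.3 SD | 4.00, rejects 41% | 3.53, rejects 37% |
| 0.5 SD | 11.11, rejects 85% | 9.80, rejects 80% |

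In simulation, the main effect rejected with SB-based above non-SB-based support in under 0.5% of runs in each of these cases.

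**Limit of the change contrast.** If the T1 gap regresses towards the mean instead of persisting, the SB group's expected excess change is gap × (1 − r) with no true effect. The contrast then falsely favours SB in 11% (r = 0.5) or 8% (r = 0.7) at a 0.3 SD gap, and in about 24% or 16% at 0.5 SD.

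**The case against.** The case for leaving the text alone has four parts.

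*The reporting sentence is general.* It closes the whole analysis section and also serves the Hypothesis 1 group ANOVAs and the regressions, where main effects are the right quantities. It does not say that only main effects will be reported, and the phrase may loosely mean principal effects. This stands. A reader might infer that the authors have declared a main effect to be the Hypothesis 3 result; the document does not say so.

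*The right test is already in the model.* Crossing time with support yields the interaction by default, and the pair of interest is one of only three that the t-tests can compare. This stands too, so it would be too strong to say that the plan cannot test Hypothesis 3. But the text ties the t-tests to means, not to change or to this pair.

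*The omnibus test is only a first step.* If both kinds of support work equally, its rejection is correct, and a pairwise follow-up should separate them. The 73% to 92% becomes a false claim only if the authors stop there, which the text does not say.

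*A baseline gap need not flatter the SB.* A reader might infer that a lower-starting SB group would appear as an SB benefit. Where higher scores are better, those rejections run against the SB.

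It could be added that an article may leave the exact contrast to a fuller plan. That would answer mere silence, but this article does state which estimates will be reported, and for Hypothesis 3 the literal reading gives the wrong ones.

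**Conclusion.** The point holds in a limited form. Taken literally, the reporting promise yields estimates that do not address the study's hypothesis on the effect of SB-informed support, and the omnibus interaction cannot support that hypothesis by itself. The correct contrast is obtainable from the planned analysis but is not named. This is a wording fault with real consequences for what gets reported; it does not make the design or model unusable.

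The firm part is the algebra: baseline gap in full, benefit in change at half size, time effect pooled over groups. The rejection rates rest on the assumed group size, correlation, effects and independence, and are illustrative. Nor is the change contrast clean in every case: it holds its 5% level only if a baseline gap persists to T2, and it does not remove confounding by who receives which support or regression to the mean among children selected by threshold.

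**What to change.** In the Hypothesis 3 paragraph of the Analysis plan:

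1. Name the Hypothesis 3 estimate as the T1-to-T2 change under SB-based support minus the change under non-SB-based support (the 1-df time-by-support contrast), reported with an effect size and 95% CI.
2. Keep the main-effects reporting for the Hypothesis 1 group ANOVAs. For Hypothesis 3, treat the omnibus interaction and both main effects as descriptive.
3. State that the Hypothesis 3 follow-up t-tests compare change.
4. Add a T1-adjusted version of the same contrast as a sensitivity analysis. It should accompany the change contrast and not replace it: the two agree when groups start level, and a divergence shows how far the result depends on whether a baseline gap persists or regresses.

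The cost is a few sentences and one extra model. No new data are needed. At 50 per group and r = 0.5, the direct contrast has 70% power for a 0.5 SD benefit of SB-based support alone, against 73% for the omnibus test, so little power is lost.
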